### Randomization

After the participant is included in the study, signed the informed consent, and participated in the baseline measurement, randomization will be carried out. Randomization will be done by an independent researcher at the University of Twente, based on a computer-generated list of random numbers.

### Description of the intervention: the online life story book

The Online Life Story Book is an e-health application that allows placing personal memories on a dynamic timeline. The timeline is easily marked with historical years. Memories like life events, anecdotes, photos, movies, voice fragments, music, recipes, preferences, and activities can be placed on the timeline. To make the application safe and warrant privacy, all information is stored on a secured server. The application is developed by Hellomydear in Belgium [33].

#### OLSB materials

The application allows storage of materials that are directly relevant to the life story of the participant. Multimedia material can be used: text, photos, movies, sound, music, and indirectly smell, taste, touch, and movement, e.g., by adding recipes or preferences for activities. Subsequently, the participant and caregiver(s) can carry out these activities. The material may consist of personal information, such as photos of the participant at school, holidays, marriage, or with family and children. Material can also be added that bears a direct relation to the life story of the participants, such as an old picture of the street where someone lived, a logo of the firm for which the participant worked, a song or piece of music the participant liked. The subjective life story of the participant provides the necessary guidance. For a participant who liked football the history of his favorite club might be documented, whereas for a person who loved technology, reminders of technological innovation could be used. The material might be in possession of the participant or informal caregivers. Sometimes, it will be necessary to digitalize these materials, which is nowadays most easily done with the use of smartphones or tablets. Digital materials can also be found in other ways. Good websites document the social-cultural history of the Netherlands and/or its regions (e.g., [34–38]). Pictures or documents available for public use can be added to the timeline. The OLSB allows including links to these online materials if they are not available for public use.

#### Making the OLSB

Trained volunteers will support persons with dementia and their informal caregivers. After a first visit to make acquaintance and draw a global time line, the volunteer will visit the participant four additional times in 8–10 weeks. The volunteers follow guidelines that are based on existing scientific and practical insights into reminiscence and dementia [39, 40]. The volunteers are trained to ask for specific memories and to make them as explicit and lively as possible. Together with the person with dementia and his or her caregiver, the volunteer searches for the themes and questions that best match the life story of the participant. The volunteer strives for a variation in themes and life phases across the four visits. After each visit, the volunteer adds memories to the timeline. After the five visits and when the online life book is completed, it will be printed to a tangible version. We expect that it will take approximately 3 months from the first visit of the volunteer to the delivery of the printed book. After the initial construction of the online life book by the volunteer, it remains possible to add memories to the timeline as well as commentaries to memories. The participant will get access for the duration of 1 year. After this year, one gets the opportunity to lengthen the registration for €10,- per year. The necessary guidelines will be made available to the participants. The person with dementia and the caregiver can allow others, like children, families, or friends to contribute to the book.

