### Employing volunteers

Given the changes in healthcare systems around the world in which more people will live longer at home instead of moving to a nursing home, not only informal caregivers but also volunteers play an increasing role and are expected to participate more and more to provide care in everyday life. For care institutes the delivery of the intervention will become more efficient than care provided by a professional [25]. For older adults, an intervention delivered by a volunteer will be less stigmatizing than care by a healthcare professional such as a psychologist, in particular while volunteers provide a new contact with society [26]. It is well-known that volunteering supports both the volunteer’s mental health and well-being and that of the people they serve [27]. Volunteers like to contribute to projects with a concrete goal, limited time investment, and possibilities for training [28]. The current project suits both altruistic and self-oriented motivations of volunteers as it offers the possibility to create something of personal value to the person with dementia and the informal caregiver, whereas it also allows them to learn new competences in the training [29, 30]. The volunteer provides the necessary structure and the needed social and technological competences that serve to ease the task for the informal caregiver. As the intervention is based on reminiscence as a naturally occurring process in later life, volunteers can easily stimulate conversations about personal memories with the help of a well-defined protocol [11].

In summary, the primary objective of the study is to assess the effectiveness of the intervention “Online Life Story Book” on neuropsychiatric symptoms of persons with early dementia, in comparison to care as usual. The study has four secondary objectives: 1) to study the effectiveness of the intervention OLSB on the burden and quality of life of the primary informal caregiver; 2) to provide a preliminary health-economic evaluation by analysing the effects on the quality of life and care consumption of the person with early dementia; 3) to study the (time to) nursing home admittance as a longer term effect; 4) to provide a process evaluation.

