## Methods and design

### Study design

A randomized controlled trial with individual randomization to one of two conditions is conducted:The intervention condition: participants in the intervention “Online Life Story Book”The control condition: participants receive care as usual.

The participant flow can be found in Fig. 1. The study takes 6 months for each individual participant with a baseline measurement (T0) as well as measurements after three (T1) and 6 months (T2). The intervention, creating an OLSB, takes about 8–10 weeks. The study takes place at the home of the person with early dementia who participates in the study. A trained volunteer will support the construction of the OLSB. Trained student assistants and the primary researcher will carry out the measurements.

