#### Sample size calculation

Based on systematic reviews [15, 17, 18], a small significant effect is expected for the primary outcome at follow-up. Hence, 74 participants are needed (GPower: f = 0.15; alpha = .05; power = .80; repeated measures anova with 2 groups and 3 measurement points; *r* = .50 between measurements). Given the vulnerability of the participants and a high mortality rate, we expect a drop-out of 30% [15, 17, 18]. Hence, 106 participants need to be included, 53 per condition.

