#### Time investment

A trained volunteer will aid the person with dementia in making the life-story book during five visits of 1 h. Based on existing reminiscence interventions [15, 17, 18], participants –and their informal caregiver and involved family– are advised to spend at least 1 h a week in using the book to recollect personal memories. Participants are instructed that this is a minimum requirement and that it is better to spend several shorter periods (e.g., 10-15 min several days a week) rather than 1 h on a separate day. Via the manual the participants also receive tips and tricks how to make use of the memories in planning everyday activities (e.g., listening to music, visiting the old primary school, baking ones favorite cookies, reading a rhyme). The time investment of these activities will vary depending on the kind of activities.

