#### Control condition

Participants in the control condition receive care as usual. They have access to all existing treatments, interventions, and support, such as medical treatment, home care, memory centers, case management, activities organized by Alzheimer Nederland, support for informal caregivers. To allow for an optimal use of usual care, participants will be informed through a booklet about existing care possibilities. Participants in the control condition are allowed to create an OLSB after the study.

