#### Effects

To analyze the effects on the primary outcome (total neuropsychiatric symptoms), repeated measures MANOVA will be used to assess the group differences across time. The condition (intervention vs. control) is the independent variable and the outcome measures across the three measurements are the repeated dependent variables. Simple contrasts will be used post-hoc to compare the post-intervention and follow-up measures with the pre-intervention measures. Effect sizes at post-intervention and follow-up will be calculated as Cohen’s d. Effect sizes between .56 and 1.2 are interpreted as large, between .33 and .55 as moderate, and below .33 as small [53].

We will also tentatively study the effects of the intervention on the four clusters of neuropsychiatric symptoms (hyperactivity, psychosis, affective symptoms, and apathy). As these measures are often not normally distributed, we will use a dichotomized outcome (clinically relevant symptoms or not, based on a FxS score of 4 and higher) [43]. We will carry out four logistic regression analyses with condition (intervention versus control) and presence of clinically relevant symptoms within the respective clusters at baseline as independent variables and presence of clinically relevant symptoms at follow-up as dependent variable. The odds-ratios will be used to provide estimates of the effect sizes in terms of Cohen’s d.

For the secondary outcome measures, three repeated measures MANOVA’s will be conducted, similar to the analysis for the primary outcome. The effect sizes will be given in Cohen’s d.

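### Volunteers deliver the intervention in one arm only, but the planned model treats participants as independent; its standard error is too small if volunteers are shared and differ in effect

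*Protocol article*

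**What the plan says.** All references are to the Protocol article.

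- **Delivery.** Making the OLSB: "Trained volunteers will support persons with dementia and their informal caregivers". Time investment: "A trained volunteer will aid the person with dementia in making the life-story book during five visits of 1 h". The volunteer looks for suitable themes together with the dyad and fills the timeline after each visit.
- **Role of the volunteer.** Employing volunteers: "The volunteer provides the necessary structure and the needed social and technological competences that serve to ease the task for the informal caregiver".
- **Standardisation.** Making the OLSB: "The volunteers follow guidelines that are based on existing scientific and practical insights into reminiscence and dementia". Volunteers are also trained.
- **Comparator.** Control condition: "Participants in the control condition receive care as usual". No trial volunteer is part of this arm.
- **Allocation.** Study design: "A randomized controlled trial with individual randomization to one of two conditions is conducted".
- **Analysis.** Effects, on the repeated measures MANOVA for the primary outcome: "The condition (intervention vs. control) is the independent variable and the outcome measures across the three measurements are the repeated dependent variables". Secondary outcomes are analysed in the same way. The Randomization check section allows adjustment for imbalanced baseline variables, but not for the volunteer.
- **Sample size.** Sample size calculation: "f = 0.15; alpha = .05; power = .80; repeated measures anova with 2 groups and 3 measurement points", with a correlation of .50 between measurements. This leads to 74 evaluable and, after 30% drop-out, 106 included (53 per condition).

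The article does not state how many volunteers there are or how many dyads each one guides.

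**The concern.** Participants are randomised one by one, but those in the intervention arm may then be grouped under volunteers. The control arm has no such grouping, so the design may be partially nested. If two dyads share a volunteer and volunteers differ in how much they help, the outcomes of those dyads are correlated. The MANOVA assumes they are not. It would then understate the variance of the intervention mean, and so the standard error of the arm difference, for the Neuropsychiatric Inventory (NPI) total and for the caregiver outcomes.

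Two things are at stake. The first is the error rate and the interval width of the main comparison, which is planned for a small effect at about 80% power and has little margin. The second is how far the result carries over to other volunteers. The Discussion looks ahead to wider use of the book and to volunteer deployment on a larger scale.

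**Working it through.** **1. Reproduce the plan's own figure.** For a repeated measures ANOVA, within-between interaction, with f = 0.15, 3 measurements and r = .50:

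- noncentrality = f² × N × 3 / (1 − r) = 0.0225 × N × 3 / 0.5 = 0.135 × N
- at N = 74: 9.99, with 2 and (74 − 2) × 2 = 144 degrees of freedom; power = 0.806
- smallest N with power of at least .80: 73, or 74 with equal arms
- drop-out: 74 / 0.70 = 105.7, so 106

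Both stated figures reproduce. The calculation contains no design effect, so it rests on independent participants.

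**2. Add volunteer clustering in one arm.** Let c be the number of dyads per volunteer and ICC the within-volunteer correlation of the outcome contrast. Neither is in the article; both are assumptions. Arms are taken as equal in size and in total variance.

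- Design effect, intervention arm: DE = 1 + (c − 1) × ICC. Control arm: 1.
- Average variance factor for the arm difference: D = (DE + 1) / 2.
- True SE / calculated SE = √D.
- Real two-sided error of a nominal 5% single contrast, when volunteer effects average to zero: 2 × (1 − Φ(1.96 / √D)).
- Power at 74 evaluable for a test with a correct standard error: noncentrality 9.99 / D, same degrees of freedom.

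Example, c = 5, ICC = .05: DE = 1 + 4 × .05 = 1.20; D = 1.10; √1.10 = 1.049; 1.96 / 1.049 = 1.869; error 6.2%.

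| c | ICC | DE | D | SE larger by | Real error | Power |
|---|---|---|---|---|---|---|
| 1 | any | 1.00 | 1.000 | 0% | 5.0% | 80.6% |
| 2 | .02 | 1.02 | 1.010 | 0.5% | 5.1% | 80.2% |
| 2 | .05 | 1.05 | 1.025 | 1.2% | 5.3% | 79.6% |
| 3 | .02 | 1.04 | 1.020 | 1.0% | 5.2% | 79.8% |
| 3 | .05 | 1.10 | 1.050 | 2.5% | 5.6% | 78.6% |
| 5 | .05 | 1.20 | 1.100 | 4.9% | 6.2% | 76.5% |
| 5 | .10 | 1.40 | 1.200 | 9.5% | 7.4% | 72.6% |
| 10 | .05 | 1.45 | 1.225 | 10.7% | 7.7% | 71.7% |
| 10 | .10 | 1.90 | 1.450 | 20.4% | 10.4% | 63.8% |

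**3. Check by simulation.** Single contrast, 40 per arm, 40,000 runs, volunteers in one arm only. The rejection rates were 5.0% (c = 1), 5.1% (c = 2, ICC .05), 6.1% and 7.1% (c = 5, ICC .05 and .10), and 7.5% and 10.2% (c = 10, ICC .05 and .10). They agree closely with the formula.

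**4. What the caseloads imply.** With 53 in the intervention arm, 5 dyads each means about 53 / 5 = 10.6, so 11 volunteers; 10 each means about 53 / 10 = 5.3, so 5.

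**The case against.** **Both inputs are assumed.** Caseload and ICC are commonly left to a full protocol or SAP, and this article is a condensed account. That stands: the absence of a caseload figure is not itself an error. What the article does fix is the model and its independent variable, and that model has no place for a volunteer effect.

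**The likely values are low.** Volunteers are trained, follow guidelines and work from a set protocol. The Employing volunteers section says they prefer a limited time commitment, which hints at small caseloads. Dyads also use the book on their own, relatives can add to it, and the NPI is answered by the caregiver. All of this should dilute volunteer differences. It stands as a reason to look first at the upper rows of the table, where the effect is minor. It does not bring the ICC to zero, and no sentence in the article limits a volunteer to one dyad.

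**The test is not simply too liberal.** A reader might infer that sharing volunteers by itself inflates the false-positive rate. The documents do not support that. Allocation is individual, so if the intervention affects nobody, the volunteers create no difference between arms and the test keeps its level. The inflated rates apply when volunteers do change outcomes but their effects average to zero.

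**The target of inference can be debated.** The stated objective is effectiveness against usual care, and treating the volunteers in the trial as fixed is defensible for that. Treating them as a sample matters for use with new volunteers. This supports a supporting analysis rather than replacing the main one.

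**Conclusion.** The point holds in conditional form. The planned MANOVA understates the standard error of the arm difference only if volunteers guide more than one dyad and also differ in effect. The effect is negligible to minor at 2 to 3 dyads per volunteer with ICC up to .05. It becomes material from about 5 dyads per volunteer with ICC of .05 or more, and reaches a 20% larger standard error and 10.4% error only at the far end of the assumed range (10 dyads, ICC .10).

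Two stronger readings should be resisted. One is that the sample size is wrong: 74 and 106 are arithmetically correct for the model stated, and the power losses in the table depend on unknown inputs. The other is that the design effect applies to the whole trial: the control arm has no volunteers, so applying it to both arms would overstate the problem.

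**What to change.** 1. Record a volunteer code for every intervention dyad, and report the number of volunteers and the spread of caseloads.
2. Keep the MANOVA, and pre-specify beside it a partially nested mixed model for the NPI total and the caregiver outcomes: a random volunteer effect in the intervention arm only, with small-sample degrees of freedom. Report whether the conclusion holds under both.
3. If each volunteer guides a single dyad, state this; the volunteer term then drops out.

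The cost is one extra variable and one extra model. If the model is run on the imputed data, the imputation should also reflect the volunteer grouping. Where few volunteers each guide many dyads (about 5 to 11 volunteers in the scenarios with a material effect), the variance component will be imprecise and the intervals may be noticeably wider. That is why it belongs beside the main analysis and not in its place. The code is easy to record during delivery and may be hard to reconstruct later.

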#### Everyday use

The use of the OLSB in everyday life is very easy and pleasant. More competences than scrolling the timeline and clicking on memories is not needed. Besides the online version that is available on a computer or tablet, every participant will receive a printed version to make it easier to use in everyday life. Codes in the book make it possible to assess online material that cannot be printed, such as sound, music, or movies. Participants and their caregivers can make use of the online or printed version to recollect personal memories of the participant. Participants and caregivers receive a manual with tips and tricks how to use the application to this end and how they can make use of the memories in their everyday contact, for example by talking about favorite memories, listening to music, or doing preferred activities.

#### Time investment

A trained volunteer will aid the person with dementia in making the life-story book during five visits of 1 h. Based on existing reminiscence interventions [15, 17, 18], participants –and their informal caregiver and involved family– are advised to spend at least 1 h a week in using the book to recollect personal memories. Participants are instructed that this is a minimum requirement and that it is better to spend several shorter periods (e.g., 10-15 min several days a week) rather than 1 h on a separate day. Via the manual the participants also receive tips and tricks how to make use of the memories in planning everyday activities (e.g., listening to music, visiting the old primary school, baking ones favorite cookies, reading a rhyme). The time investment of these activities will vary depending on the kind of activities.

#### Control condition

Participants in the control condition receive care as usual. They have access to all existing treatments, interventions, and support, such as medical treatment, home care, memory centers, case management, activities organized by Alzheimer Nederland, support for informal caregivers. To allow for an optimal use of usual care, participants will be informed through a booklet about existing care possibilities. Participants in the control condition are allowed to create an OLSB after the study.

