#### Longer term outcome

##### Nursing home admittance

The longer term outcome is (time to) admittance to a nursing home. This will be assessed for all participants in month 18 of the study together with the general practitioner.

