##### Nursing home admittance

The longer term effect of (time to) nursing home admittance will be analyzed by comparing the intervention and control condition in a Cox’s hazard regression analysis.

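### As written, controls may create an OLSB before the month-18 nursing home comparison, and the article neither ties down the timing nor records such use

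*Protocol article*

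**What the plan says.** All references are to the protocol article.

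- *Study design*: "The study takes 6 months for each individual participant", with measurements at baseline (T0), 3 months (T1) and 6 months (T2).
- *Control condition*: "Participants in the control condition are allowed to create an OLSB after the study". No waiting time or expected uptake is given.
- *Longer term outcome, Nursing home admittance*: "This will be assessed for all participants in month 18 of the study together with the general practitioner". The section does not say whether month 18 is counted from each participant's baseline or from the start of the project.
- *Statistical analyses, Nursing home admittance*: the outcome "will be analyzed by comparing the intervention and control condition in a Cox’s hazard regression analysis". Crossover is not mentioned.
- The objective is stated at the end of *Employing volunteers*: "3) to study the (time to) nursing home admittance as a longer term effect".
- *Reminiscence Activities* and Table 1: caregivers are asked about reminiscence activities, including whether a control made a book, at T1 and T2 only.
- *Making the OLSB*: "We expect that it will take approximately 3 months from the first visit of the volunteer to the delivery of the printed book".

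**The concern.** If the study ends for a participant at month 6, a control may take up the intervention from then on and still be analysed as a control at month 18. From that point the contrast moves from OLSB versus care as usual towards OLSB now versus OLSB later. A real effect on admittance would then look smaller than it is. Nothing in the article would show how far this had happened, because no question about OLSB use is asked after T2. A null result on the third secondary objective could be read as no longer-term benefit when part of the control arm had received the same book.

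**Working it through.** **The plan's own figures.** The article gives no event number, target hazard ratio or power for nursing home admittance. Its sample size concerns the NPI and reproduces: for the group-by-time interaction with f = 0.15, three measurements and r = 0.50, the smallest even total with at least 80% power is 74 (power 0.806), and 74 / 0.70 = 105.7, hence 106, or 53 per arm. Only the 53 per arm is used below.

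**1. How much of the window is open to crossover?**

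- Month 18 counted from baseline, access from month 6: (18 − 6) / 18 = 12/18 = 67%.
- The same, but counting from a finished book, about 3 months later: (18 − 9) / 18 = 9/18 = 50%.
- Month 18 as a project month: a participant entering in project month e is followed for 18 − e months, of which 12 − e (or none) fall after month 6. Entry at month 0 gives 12 of 18, entry at month 6 gives 6 of 12, and entry at month 12 gives 0 of 6. The entry months are illustrations.

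These shares are ceilings, because the article permits uptake and does not say how much there will be.

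**2. How much would the hazard ratio move?** Assumptions, none of them in the article: constant hazards, a true hazard ratio h = 0.70, and a share u of controls who take on the intervention hazard at month s. After month s the hazard ratio is h / (1 − u + u·h). Weighting by time,

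ln HR(average) = (s/18)·ln h + ((18 − s)/18)·ln[h / (1 − u + u·h)].

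| Uptake u | HR after month s | Average, s = 6 | Average, s = 9 |
|---|---|---|---|
| 0% | 0.70 | 0.70 | 0.70 |
| 25% | 0.70/0.925 = 0.757 | 0.74 | 0.73 |
| 50% | 0.70/0.85 = 0.824 | 0.78 | 0.76 |
| 100% | 1.00 | 0.89 | 0.84 |

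For example, at 50% uptake and s = 6: (1/3)(−0.357) + (2/3)(−0.194) = −0.248, and exp(−0.248) = 0.78.

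**3. Does power matter here?** With a stronger assumed effect (true hazard ratio 0.5), 53 per arm, an assumed 18-month control risk of 20%, and event-weighted averaging, Schoenfeld's formula gives power = Φ(|ln HR|·√(D/4) − 1.96):

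- no uptake: D = 16.2, HR 0.50, power 0.29
- 50% uptake at month 6: D = 14.6, HR 0.60, power 0.16
- 100% uptake at month 6: D = 12.9, HR 0.735, power 0.08

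The comparison is weak even without crossover.

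**4. What does stopping at month 6 cost?** Under the same assumptions and no uptake, expected events to month 18 are 53 × [0.20 + (1 − 0.8^(1/2))] = 16.2, and to month 6 they are 53 × [(1 − 0.8^(1/3)) + (1 − 0.8^(1/6))] = 5.7. The loss is 1 − 5.7/16.2 = 65%. Over assumed control risks of 10% to 50% the loss is about 66% to 60%.

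**The case against.** The strongest objection is that the article uses *the study* in two senses. A study of 6 months per participant has no month 18, whereas the nursing home section speaks of a study that does. If that wider sense governs the *Control condition* section, controls wait until after month 18 and there is no crossover. If month 18 is a project month, time after T2 is shorter and could be nil for late entrants. This stands as a reason to keep the point conditional. It does not remove it: *Study design*, the 6-month window of the health-economic evaluation, the T1 and T2 coverage of *Reminiscence Activities*, and the *Discussion* all use the 6-month span, so the text needs reconciling under either reading.

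It is also fair that permission is not uptake, that a book takes about 3 months to produce, and that a comparison as randomised remains a valid comparison of the initial offer. Dilution would be towards no difference and would not be expected to create a false benefit.

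Two stronger readings are tempting. A reader might infer that most of the comparison is diluted. The documents do not support this: 12 of 18 months is the most that could be affected, and uptake is unknown. A reader might also fault the absence of a rule for deaths, since *Sample size calculation* expects high mortality. Handling of death and censoring is commonly left to the analysis plan, which is not shown, so its absence here is no finding. A Cox model that censors at death already estimates the cause-specific hazard ratio.

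**Conclusion.** The point holds in a conditional form. On the article's own 6-month definition, controls may receive the intervention before the month-18 comparison, and any such use after T2 goes unrecorded. If month 18 runs from baseline, up to 12 of 18 months are exposed, or about 9 of 18 from a finished book. With an assumed true hazard ratio of 0.70, the average could lie anywhere from 0.70 (no uptake) to 0.89 (all controls at month 6), or up to 0.84 if the effect starts at month 9. At low uptake the shift is small. The matter touches one secondary, longer-term objective. The NPI analysis at T1 and T2 is unaffected. It should be corrected because crossover dates that are not collected may not be recoverable at analysis.

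**What to change.** 1. Reconcile *Study design*, *Control condition* and *Nursing home admittance*: state the origin of month 18, and when controls gain access to an OLSB relative to it.
2. At the month-18 contact, record for each control whether and when an OLSB was started. The practitioner may not know this, in which case the caregiver would have to be asked.
3. Keep the Cox comparison as randomised. If controls gain access before month 18, report it as immediate versus delayed access and not as OLSB versus care as usual.
4. Add a sensitivity analysis with all participants censored at month 6.

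The cost is one extra date per control and some wording. The month-6 analysis would lose about 60% to 66% of expected events under the assumptions above. It also covers only about 3 months after a book is delivered, so it supports the main comparison and cannot replace it. If month 18 is at present a project month, redefining it from each baseline would lengthen follow-up for later entrants. Stating the origin is the minimum and costs nothing.
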